### Participant timeline {13}

See Table 1.

**Table 1 Tab1:** Activity scheme

	**Screening**	**Enrolment**	**Intervention**	**End of intervention**	**Short-term endpoint assessment**	**Mid-term endpoint assessment**	**Long-term endpoint assessment**
**Date**	x	x	x	x	x		
**Informed consent document**	x						
**Signed informed consent document**		x					
**Eligibility**	x						
**Demographic and perinatal data**		x					
**Parental data**		x					
**NICU facilities**		x					
**FICare profile**		x					
**Day of life and PMA**		x		x	x	x	x
**Neonatal outcomes**					x		
**Task on training**			x	x			
**Kangaroo (hours/week)**			x				
**Weight, length, head circumference**		x	x	x	x	x	x
**Nutrition**				x	x	x	
**Maturation skills**				x	x		
**Adverse events**			x	x	x		
**Reason for early discontinuation**				x			
**General health**						x	x
**Neurodevelopment**							x
**Economic impact**^a^			x	x	x		x
**Parental questionnaires**		x			x	x	
**Staff questionnaires**^b^							

X indicates mandatory procedures that should be entered into the eCRF

*NICU* neonatal intensive care unit, *FICare* Family Integrated Care, *PMA* postmenstrual age

^a^Economic impact on newborns, carers and staff as described in Additional file 1

^b^2 measurement points: first time before FICare implementation at his/her institution; second time at least 3 months after FICare implementation at his/her institution. In FICare expert centre only one time

### Sample size {14}

No previous study has assessed the effect of FICare intervention on growth velocity expressed in g/kg per day. Therefore, for sample size calculation in the RISEinFAMILY project, we will follow one of the most recent studies evaluating the effect of individualised breast milk fortification on weight gain expressed in the same units [34]. In this study, based on their own data obtained in a pilot and other literature data, the authors assumed 1.8 ± 3.1 g/kg/d as a reasonable and clinically meaningful difference in weight gain. With a total *N* of 103 (experimental group *N* = 52, control group *N* = 51), they found a difference in the weight gain of 1.9 g/kg/d and a standard deviation of 2.5 g/kg/d.

Using this information, we calculated the minimum size for the intervention (FICare) and the control (standard care) group in the RISEinFAMILY study. Our null hypothesis is no impact of FICare and, as a consequence, the mean of the weight gain in both the intervention and control groups will be the same. Our alternative hypothesis is a difference in the mean weight gain between FICare and the control group of at least 1.9 g/kg/d [34]. We impose a type I error (probability of rejecting the null hypothesis when it is true) of 5% (*α* = 0.05), and a type II error (probability of not rejecting the null hypothesis when it is false) also of 5% (> 0.05), which provides a statistical power of 95%. The minimum sample size for intervention and control groups is given by at least 46 children in the intervention (FICare) and other 46 children in the control (standard care) group.

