### Trial design {8}

This quality improvement project is designed as an international, multi-centre, pluri-cultural prospective stepped-wedge cluster controlled trial. Five non-FICare-experienced NICUs from Netherlands, Turkey, Romania, the UK and Zambia (sites 1–5) and two clinical sites who have recently implemented FICare from Spain and Netherlands (sites 6 and 7) are expected to be recruiting infants into this trial that will include at least 552 babies during a 32-month period (see Fig. 1). The stepped wedge cluster design was selected due to the nature of the intervention, which involves changes to unit-level provision of care and interaction between participants, with a risk of cross-contamination.

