#### Intervention description {11a}

The study will start at the same time at all participating sites that will continue to provide routine clinical care according to their current policies. Prospective data gathering will be accomplished.

A start point for the experimental intervention (3, 6, 9, or 12 months from the start of the study) will be assigned for each clinical site (1 to 5) taking into account the expected time internally needed to overcome all logistics and regulatory issues with a potential impact on FICare implementation. A 3-month wash-out period will be used for the local training process and assessment of site readiness, while enrolment will be halted. After that, recruiting will continue, and the experimental intervention will be started. Clinical sites 6 and 7 will run the experimental intervention from the start of the study, without pauses.

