## Assignment of interventions: blinding

### Who will be blinded {17a}

Given the logistical and regulatory challenges in implementing randomization at clinical sites 1 to 5, blinding is not feasible. This is due to variations in hospital size and the internal time required to address logistical and regulatory issues. The primary objective remains the achievement of an equitable distribution of patients between the control and intervention groups. Consequently, hospitals and healthcare professionals involved in this trial will not be blinded for the assigned trial protocol.

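### The 95% power claimed for 46 + 46 infants is that of two independent samples, not of this trial's stepped-wedge comparison, and it is not linked to the planned 552

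*Protocol article*

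**What the plan says.** Sample size {14} takes a trial of individualised milk fortification as its source. It reports that trial's planning values (1.8, SD 3.1 g/kg/d) and its observed values (1.9, SD 2.5). The null is that "the mean of the weight gain in both the intervention and control groups will be the same"; the alternative is "a difference in the mean weight gain between FICare and the control group of at least 1.9 g/kg/d". With 5% type I and 5% type II error, the section concludes: "The minimum sample size for intervention and control groups is given by at least 46 children in the intervention (FICare) and other 46 children". Cluster, step, calendar period and the trial's total enrolment do not appear there.

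Trial design {8} says the trial will "include at least 552 babies during a 32-month period" at seven sites. Intervention description {11a} sets the timetable for sites 1–5: "A start point for the experimental intervention (3, 6, 9, or 12 months from the start of the study", then a 3-month halt in enrolment, then intervention. Sites 6 and 7 are on intervention throughout. Who will be blinded {17a} adds: "The primary objective remains the achievement of an equitable distribution of patients between the control and intervention groups".

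Statistical methods {20a} takes the intervention effect from the centres without FICare experience, that is sites 1–5. It analyses weight gain over four weeks by GLMM with gestational age and site forced in. No calendar-time term is named there; the Discussion says only that the analysis takes time into account.

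**The concern.** In a stepped wedge every site moves from control to intervention as calendar time passes, so treatment and secular trend are entangled by design. Separating them costs precision, and a formula for two independent groups does not count that cost. It also assumes equal groups, which the start schedule does not by itself deliver. A reader would take 95% as the power of this trial, and a null result would then be read as strong evidence against a 1.9 g/kg/d effect when the comparison behind it may be much less precise.

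**Working it through.** **1. The plan's own figure.** Inputs from Sample size {14}: difference 1.9, SD 2.5, α 0.05, power 0.95. Two-sided is inferred, because one-sided gives 38.

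- Normal formula: n = 2(1.960 + 1.645)² × 2.5² / 1.9² = 2 × 12.995 × 6.25 / 3.61 = 45.0 per group.
- Two-sample t test: power 0.9458 at 45 and 0.9501 at 46. So 46 per group is reproduced exactly.
- With the source trial's planning pair (1.8, SD 3.1), 46 per group gives 79% power, and 95% needs 79 per group.

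**2. Allocation implied by the timetable.** Over 32 months less a 3-month pause, each of sites 1–5 enrols for 29 months, giving 5 × 29 = 145 site-months. Four sites starting at 3, 6, 9 and 12 months have 30 control months. The fifth, whose start is not given, adds 3 to 12, so control time is 33 to 42 site-months.

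- 33/145 = 23% and 42/145 = 29%.

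At even enrolment over the whole 32 months, that is the control share in sites 1–5, against the 50% assumed.

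**3. Power with calendar adjustment.** The treatment-effect variance was obtained by generalised least squares on site-by-period means, with a treatment term, a random site effect, and either 3-month period effects or a linear trend. Power = Φ(difference/SE − 1.96).

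Assumptions, none given in the article:

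- ICC 0 to 0.10 and cluster autocorrelation 0.8;
- 11 three-month periods, the second site on a shared step placed at 3, 6, 9 or 12 months;
- enrolment either even over time or equal between conditions within site;
- 460 infants in sites 1–5 (5 × 92), leaving 92 of the 552 for sites 6–7.

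| Infants and sites | Calendar time | SE | Power, 1.9 / SD 2.5 |
|---|---|---|---|
| 92, sites 1–5, 1:1 within site | none | 0.51–0.52 | 95–96% |
| 92, sites 1–5 | linear trend | 0.93–1.07 | 43–54% |
| 92, sites 1–5 | 3-month periods | 1.39–1.77 | 19–28% |
| 460, sites 1–5 | linear trend | 0.41–0.51 | 96–99% |
| 460, sites 1–5 | 3-month periods | 0.62–0.86 | 60–86% |
| 552, sites 1–7 | 3-month periods | 0.42–0.52 | 95–99% |

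Example: SE 1.77 gives 1.9/1.77 − 1.96 = −0.89, and Φ(−0.89) = 0.19.

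The first row shows that site clustering alone does not lower the power; calendar adjustment does. The loss at 92 infants is present at ICC 0. With 1.8 and SD 3.1, the last two rows become 39–64% and 79–93%.

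**4. Sensitivity.** A calendar of only 7 periods raises the 92-infant, period-adjusted figure to at most about 41%. If the 552 accrue evenly over seven sites, sites 1–5 hold 552 × 5/7 = 394 infants; over 7 or 11 periods and ICC 0.01–0.10, power is then 63–93%. With only five crossing sites the normal approximation is optimistic, so a small-sample correction would lower all these figures.

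**The case against.** Several objections are sound and limit the point.

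- **46 + 46 is not miscalculated.** It is right for its formula. The fault is the match between formula and design.
- **Nobody plans to stop at 92.** It is called a minimum, and the plan is at least 552. A reader might infer from 19–28% that the trial is underpowered. The documents do not support that: at the planned scale the result runs from 60% to 99%, depending on how time is modelled and whether sites 6–7 contribute.
- **The written model names no calendar term.** The benchmark is therefore what a stepped wedge needs, together with the Discussion's remark on time; it is not a contradiction of a written period-adjusted model. It also uses one value per infant, not the weekly measurements. Still, 95% is recovered only by assuming no secular trend, and the article does not claim that.
- **The origin of 552 is unknown.** It equals 12 × 46 = 5 × 92 + 2 × 46, and a reader might infer that each site was sized as its own before–after study. Nothing in the article says so, Fig. 1 is not shown, and a derivation may stand in the full protocol. What can be said is that the Sample size section does not make the link.
- **1:1 is not impossible.** The 23–29% share depends on even enrolment. Hospitals differ in size, and starts are assigned with balance in mind. The timetable makes 1:1 an assumption that needs support; it does not rule it out.
- **Using 1.9 and 2.5 is disclosed.** Both pairs are printed, and choosing the observed one is defensible. The other pair belongs in a sensitivity case; its omission is not evidence of selective planning.

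**Conclusion.** The point holds in this limited form. The stated 95% is the power of a two-sample t test with 46 per group, and it should not stand as a property of this stepped-wedge trial. For 92 infants in sites 1–5 the calendar-adjusted power is about 19–28% with 3-month periods and 43–54% with a linear trend, and this shortfall does not depend on the ICC. At about 460 infants in sites 1–5, the sites on which {20a} bases the intervention effect, it is 60–86% or 96–99%. Under period adjustment, about 95% or more is reached across the assumed ICC range only when sites 6–7 inform the calendar effects (95–99% at 552). The direction is firm. The exact figures rest on the assumed ICC, autocorrelation, period length, accrual and split of the 552. No inadequacy of the 552 is shown.

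**What to change.** Rewrite the Sample size paragraph:

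- withdraw the 95% claim for 46 + 46;
- state the power, at the planned 552, of the pooled model adjusted for site and calendar time, and say how time enters (periods or trend);
- show how 552 arises, with the control and intervention numbers expected from the start schedule;
- give a range of ICCs, with 1.8 and SD 3.1 as a sensitivity case.

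Compute this power for sites 1–5, since {20a} bases the intervention effect on them. If sites 6–7 are meant to inform the calendar effects, amend {20a} to say so and name the assumption this brings: a secular trend common to all seven sites.

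The cost is one rewritten paragraph, possibly one sentence in {20a}, and perhaps a lower stated power. No extra enrolment is needed.

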### Recruitment {15}

This is a stressful time for parents and families. Coping with all the information provided at this early stage is difficult for parents. For this reason, a strategy for recruitment is in place to avoid overloading parents with information during the critical period after birth when they are most vulnerable:Prior to any enrolment, information about the RISEinFAMILY project will be made public in participating hospitals through leaflets, posters, and the use of modern technology.Whenever possible, a summary with preliminary information about the programme will be distributed to parents of potential candidates antenatally, in order to provide them with more time to think about joining the study if the baby and family become eligible after birth. Contact information for the local quality improvement team will be provided.Whenever possible, parents will give written informed consent antenatally after an explanation of the aims, methods, benefits and potential hazards of the programme. The implications of the programme’s intervention to the neonates and families enrolled should be clearly explained by the local research team as part of the informed consent process. Perinatal committees are the ideal forum to comment on potential candidates. These committees are the forum where complicated pregnancies are discussed among obstetricians and neonatologists. Appointment with eligible families can be scheduled according to the information gathered in these meetings, allowing a full explanation of the RISEinFAMILY project before delivery.Parents that have not yet given written informed consent for the study will be approached as soon as possible after the baby is born and admitted to the NICU and provided with the relevant parental information.

## Assignment of interventions: allocation

### Sequence generation {16a}

In this non-randomized study, the allocation sequence is not generated using computer-generated random numbers. Instead, the allocation is based on considerations aimed at achieving an equitable distribution of patients between the control and intervention groups.

### Concealment mechanism {16b}

For the study at clinical sites 1-5, the initiation involves a control phase where standard neonatal care procedures are followed. Subsequently, during the wash-up period, the implementation of the intervention begins. The concealment mechanism is considered not applicable in this context.

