### Interventions

#### Explanation for the choice of comparators {6b}

A cohort of patients, born at clinical sites 1 to 5 from the beginning of the study to the time assigned to start the intervention, will be assigned to the control group, representing standard neonatal care.

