For our primary hypothesis, we will compare infant standardised weight gain velocity between the two groups over the 4-week study period using generalised linear mixed modelling (GLMM). For our primary outcome, we will compare infant standardised weight gain between the two groups over the study period defined as the change in Patel’s growth pattern measured weekly from enrolment until day 28 post-enrolment, testing an interaction term between group and post-baseline weight measurements. We will adjust for additional covariates using a hybrid approach, forcing in known confounders of gestational age and study site and using backward stepwise selection to retain covariates that contributed *p* < 0.1 to the final model from potential confounders. Additionally, we will conduct sensitivity analyses by adding in weight measured at discharge.

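### Control infants enrolled in the last 28 days before the training wash-out have growth measured during it and counted as standard care, and the article conflicts on when the intervention begins

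*Protocol article*

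**What the plan says.** Four statements in the protocol article, read together, fix what counts as control data at the five crossover sites.

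- **Who is control.** Explanation for the choice of comparators {6b}: infants born at sites 1–5 "from the beginning of the study to the time assigned to start the intervention, will be assigned to the control group". Status follows birth date. Nothing is said about where an infant's follow-up falls.
- **What the wash-out stops.** Intervention description {11a}: "A 3-month wash-out period will be used for the local training process and assessment of site readiness, while enrolment will be halted". The next sentence starts the experimental intervention once that period is over. Implementation {16c} adds that data collection continues throughout.
- **How long growth is measured.** Statistical methods {20a}: "measured weekly from enrolment until day 28 post-enrolment", with discharge weight added in sensitivity analyses. Outcomes {12} instead defines adequate growth over the NICU admission.
- **When implementation begins.** Concealment mechanism {16b}: "Subsequently, during the wash-up period, the implementation of the intervention begins". I take wash-up and wash-out to be the same period, as no other fits.

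Trial design {8} says the stepped-wedge design was chosen because care changes at the level of the unit and participants could contaminate one another.

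**The concern.** A control infant enrolled within 28 days of the start of the wash-out has not reached day 28 when training begins. Later weekly weights are taken on a unit whose staff are learning the new model. Training and certification aims to reach 90% of NICU staff and covers involving families, bonding and family-centred rounds. Under the stated rules these weights remain control data, and nothing in the article sets them aside. If practice shifts during training, exposed time is counted as standard care, which would pull the comparison towards no difference.

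The timing conflict makes this harder to judge. {11a} puts the start of the intervention after the wash-out, while {16b} puts the beginning of implementation inside it. {6b} closes the control cohort at the assigned start, and {11a} does not make clear whether month 3, 6, 9 or 12 is the beginning or the end of the wash-out. These dates define the two arms. In a trial without random allocation or blinded staff, they should not be left to be settled after the data are seen.

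**Working it through.** **The plan's own figure.** From Sample size {14}: the alternative is "a difference in the mean weight gain between FICare and the control group of at least 1.9 g/kg/d", and for the standard deviation the article reports that in the cited fortification trial "they found a difference in the weight gain of 1.9 g/kg/d and a standard deviation of 2.5 g/kg/d". Type I error is 5% (sidedness not stated) and power 95%.

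n per group = 2 × [SD × (z₀.₉₇₅ + z₀.₉₅) / δ]² = 2 × [2.5 × (1.960 + 1.645) / 1.9]² = 45.0, so 45. The two-sided t-test version gives 45.98, so 46, which matches the stated 46 per group. A one-sided test gives 38 and does not match. Normal-approximation power at 46 per group is 95.4%.

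**Overlap per site.** Assume even enrolment, follow-up of every infant to day 28, and a wash-out that starts at the assigned month. With 30.44 days per month, a control phase of T months lasts D = 30.44 × T days.

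- Share of controls with any overlap = 28 / D.
- An infant enrolled u days before the wash-out (u < 28) has 28 − u exposed days. Averaged over u, that is half the window, so the share of control follow-up exposed = 14 / D.

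| Control phase (months) | D (days) | Any overlap | Follow-up exposed |
|---|---|---|---|
| 3 | 91.3 | 30.7% | 15.3% |
| 6 | 182.6 | 15.3% | 7.7% |
| 9 | 273.9 | 10.2% | 5.1% |
| 12 | 365.3 | 7.7% | 3.8% |

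**Pooled.** There are five sites and four start points. Assume each start point is used once, the fifth site repeats one of them, and monthly enrolment is equal across sites. Control time is then 3 + 6 + 9 + 12 = 30 months plus 3 to 12, or 33 to 42 site-months.

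- Any overlap: (5 × 28) / (33 × 30.44) = 13.9%, down to (5 × 28) / (42 × 30.44) = 11.0%.
- Follow-up exposed: half of these, 7.0% down to 5.5%.

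**Effect on the contrast.** Let k be the fraction of the full effect that acts during the wash-out, in proportion to exposed days, and s the exposed share. Then δ = 1.9 × (1 − k × s).

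| k | s | δ (g/kg/d) | Power at 46 per group | n per group for 95% power |
|---|---|---|---|---|
| 1 | 5.5–7.0% | 1.80–1.77 | 93.1–92.4% | 51–52 |
| 0.25 | 5.5–7.0% | 1.87 | 94.9–94.8% | 47 |
| 1, every control phase 3 months | 15.3% | 1.61 | 87.0% | 63 |

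The last row is an extreme bound, not the planned layout. All power figures use the plan's individual-level formula without clustering, so only the change relative to 95.4% is informative.

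**The other reading of the start points.** If the wash-out ends at the assigned month, control phases last 0, 3, 6 and 9 months. A 3-month site then has no control phase, which does not fit {16c}, where every cluster contributes to both periods. The remaining sites have 30.7%, 15.3% and 10.2% of controls with any overlap.

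**Longer windows.** For growth over the whole admission, or outcomes to discharge, the overlap is larger. It cannot be computed, because no length of stay is given.

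**The case against.** The case against is substantial.

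- **The two timing statements may be compatible.** If implementation in {16b} means staff training and readiness checks, it agrees with {11a}. Family education is a separate curriculum, delivered task by task at the cot-side, and consent precedes the intervention. No section says control families receive it. This stands: the documents firmly support staff training in the window, while delivery to families would rest on {16b} alone. The conflict still has to be resolved in the text.
- **The effect is small and conservative.** A bias towards no difference does not flatter a superiority claim, and the percentages with any overlap include infants with a single exposed day. This also stands, so the exposed share of follow-up (5.5–7%) is the better measure.
- **Handling of transition data is often left to the analysis plan.** That is true of coding detail. The dates on which control status ends and the intervention begins are design definitions, however, and the article states them in conflicting ways.
- **Leaving weeks out shortens follow-up in controls only.** This is a fair caution. It could leave a classification of growth over the whole admission incomplete. In the weekly model the cut is set by a calendar date, not by the infant's course, and a sensitivity analysis retaining those weeks shows whether it matters.

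**Conclusion.** The concern holds in a limited form. At all five crossover sites, controls enrolled in the last 28 days before the wash-out supply some growth data during staff training, and the stated rules count those data as standard care. About 11–14% of pooled controls have any overlap, and about 5.5–7% of pooled control follow-up is exposed. The likely bias is modest and towards no difference: the 1.9 g/kg/d contrast falls to about 1.77–1.80 if the full effect acted during the wash-out, and hardly changes if a quarter did.

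These figures assume even and equal enrolment, a wash-out starting at the assigned month, all four start points in use, and follow-up of every infant to day 28. Eligibility requires only an expected stay of at least 7 days, so earlier discharge would lower them.

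A reader might infer more than this:

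- That the whole comparator is contaminated. It is not: an infant enrolled more than 28 days before the wash-out has completed the 28-day outcome, even if still on the unit.
- That staff learn kangaroo care in this window, biasing kangaroo hours directly. The staff modules listed do not name it; it appears as an outcome and in the activity table.

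**What to change.** 1. Reconcile {6b}, {11a} and {16b}. State that the control cohort closes at the start of the wash-out, give one date per site that defines when the intervention starts, and say whether month 3, 6, 9 or 12 is the beginning or the end of the wash-out.
2. Record the training-start date for each site in the eCRF.
3. Code control infant-weeks after that date as transition and leave them out of the control data in the weekly mixed model.
4. Add a sensitivity analysis that retains those weeks as control.

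The cost is wording in the protocol and analysis plan, one site-level date, and about 5.5–7% of control infant-weeks in the 28-day window. Recruitment is not affected, because enrolment is already halted in this period.
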